### Objectives

Specific objectives are as follows:

1. To assess recruitment and retention rates to inform a future definitive RCT

2. To estimate the effect size for an appropriate primary study outcome in a future definitive RCT

3. To determine the success of different patient recruitment methods (community recruitment, primary care and secondary care)

4. To identify the constituents of 'usual care' for gluteal tendinopathy in an Irish context and to determine if inclusion of a usual care arm in a future definitive RCT is feasible and appropriate without the potential for co-intervention bias

5. To assess outcome measure completion

6. To assess the feasibility of collecting healthcare utilisation and cost data for cost-effectiveness analysis

7. To assess if adherence to the home exercise programme (HEP) for those allocated to the EDX-Ireland intervention differs when recorded
*via* a smartphone application compared with paper diaries

8. To assess the acceptability of the EDX-Ireland intervention and usual care from the perspective of study participants and service providers (treating therapists and providers of usual care)

9. To assess participants’ and therapists’ acceptability of a smartphone-based application (app) for exercise provision and home exercise adherence recording in the EDX-Ireland arm

10. To compare EDX with usual care on clinical outcomes including pain, function, hip abductor muscle strength, psychological measures, and quality of life.

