### Randomisation and concealed allocation

The randomisation schedule will be generated using a computer-generated random sequence in advance of trial commencement by the trial statistician (KB), who will not be involved in recruitment or outcome assessment. Randomisation will be stratified by recruitment method (GP, secondary care or community/social media). Participants will be randomly allocated (1:1 ratio) using random blocks of size 2, 4, 6, or 8 within each stratum. Within the intervention arm (n=32) a further 1:1 blocked randomisation (block size 2, 4 or 6) will be developed for random allocation of the EDX-Ireland group, within the SWAT, to either the smartphone application (n=16) or paper-based diaries (n=16). Randomisation and allocation will be done by the PI ([name]), who will not be involved in screening or baseline assessment of trial participants, thus maintaining concealed allocation.

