### Outcomes measures

**
*Primary outcome measures.*
** Primary outcomes focus on feasibility issues including success of recruitment and retention to the 3-month time point. Details of feasibility outcomes and methods used to collect these outcomes are outlined in
Table 3.

**Table 3. T3:** Feasibility outcomes.

Objective	Data collection method
To assess recruitment rates and determine the success of different patient recruitment methods community recruitment, primary care and secondary care) To assess short (8-week) and medium-term (3-month) retention rates	• Number of individuals who contact the research team about the trial (community recruitment) • Recruitment source of each person who undergoes screening process • Number who do/do not consent to telephone screening • Number who are eligible/ineligible to proceed to physical screening • Number who are eligible/ineligible to proceed to MRI • Number who are eligible/ineligible based on MRI findings • Number who are eligible based on MRI findings but decline to participate • Number who consent to participate in the study • Number randomised to participate in the study • Number who attend for 8-week and 3-monthfollow-up • Number who cannot be contacted • Number who do not attend • Number who cannot attend/cancel follow-up (reasons)
To identify the constituents of ‘usual care’ and to determine if inclusion of a usual care arm is feasible and appropriate without the potential for co- intervention bias	Referral sources will be asked to complete a checklist of usual care options (including medications, referral for physiotherapy/other healthcare services). This will be cross-referenced against the participant-completed health and cost questionnaire. Participants will also complete details on current and past treatment for gluteal tendinopathy at baseline assessment.
To estimate the effect size for a likely primary study outcome in a future definitive trial	Based on clinical outcomes collected at 8 weeks and 3 months
To determine outcome measure completion	Completion rate of clinical outcomes collected at baseline, 8 weeks and 3 months

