### Statistical analysis

Descriptive analysis will include proportions and 95% confidence intervals (CI), means and standard deviations (SD) or medians and inter-quartile ranges (IQR) where appropriate. Feasibility outcomes of recruitment and retention rates will be descriptively reported overall across both arms of the trial (percentages and 95% CIs) and by method of recruitment. Outcome measure completion will be described both by participant and by outcome measure using percentages. Recruitment rates will be calculated as the number of participants who consent to participate divided by the number of eligible participants approached. Trial retention rates will be calculated from the number of participants who complete all outcome measures divided by the number who record baseline outcome measures. Adherence rate of exercises within the SWAT for the EDX group, and types of usual care for the control group will be reported as percentages.

Results of secondary clinical outcomes including NPRS, hip abduction strength and measures of psychological distress will be reported using means and SD or medians and IQR, where appropriate for baseline, 8- and 3- month follow-up. Statistical analysis will be performed using Stata v18 (StataCorp, College Station, Texas, USA).

Sensitivity analysis will be conducted as a secondary analysis to impute any missing data using multiple imputation. The resource use data captured by the OCC-Q will be valued using unit costs derived from local and national sources and will be analysed in a manner consistent with the clinical outcome data.

Qualitative data from interviews will be transcribed verbatim. A two-stage analysis will be undertaken, initially through inductive line-by-line coding of the extracted results to identify emergent themes, followed by deductive mapping of pre-identified codes to the Theoretical Framework of Acceptability (
Sekhon *et al.*, 2017).

Trustworthiness will be attained through procedures such as member checking, maintaining a reflexive journal of the research procedures and a clear audit trail of the process (
Braun & Clarke, 2014).

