### Sample size

We will aim to recruit 64 participants. A sample of 60 participants (n=30 per arm of the trial) would provide an estimate of the recruitment rate of ≥50% (95% confidence interval (95% CI) 37.3% to 62.7%), and an estimated retention rate of ≥80% (95% CI of 69.8% to 90.2%). To ensure balance within each stratum, sample size will be increased to 64 with 32 allocated to each arm. This sample size will also allow for the potential effect of the primary outcome (GROC) between the two groups to be determined for powering a larger definitive trial.

Study status: is currently ongoing. The expected end date for the study is January 2025.

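### Clinical outcomes are planned only as summaries by visit, although Objectives 2 and 10 call for a between-group effect; a difference with 95% CI should be stated, using the baseline values and strata already held.

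*Protocol article*

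**What the plan says.** Three places in the protocol article promise a between-group result.

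- Objectives, item 10: "To compare EDX with usual care on clinical outcomes including pain, function, hip abductor muscle strength, psychological measures, and quality of life".
- Objectives, item 2: "To estimate the effect size for an appropriate primary study outcome in a future definitive RCT". Table 3 (Outcomes measures) gives only a data source for it: "Based on clinical outcomes collected at 8 weeks and 3 months".
- Sample size: "This sample size will also allow for the potential effect of the primary outcome (GROC) between the two groups to be determined for powering a" (the sentence ends by naming the definitive trial).

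The Statistical analysis section is the only text on method. For clinical outcomes it says "Results of secondary clinical outcomes including NPRS, hip abduction strength and measures of psychological distress will be reported using means and SD", with medians and IQR as the alternative, at each visit. It does not say that these summaries are split by arm, names no difference, interval or model, and does not mention GROC. Multiple imputation is planned as a sensitivity analysis, without naming the estimate whose sensitivity is to be examined. Cost data are to be handled in the same way as the clinical outcomes.

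Two sources of information are available at analysis. The patient-reported outcomes and abductor strength are measured at baseline (Procedure). In addition, "Randomisation will be stratified by recruitment method (GP, secondary care or community/social media"). In the analysis text the recruitment method appears only for recruitment and retention rates.

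**The concern.** A set of summaries by visit is not the comparison that Objective 10 names, and it is not an effect estimate with its uncertainty, which is what Objective 2 needs. The section is not brief across the board: it defines numerators and denominators for recruitment and retention, attaches confidence intervals to those rates and specifies imputation. For the clinical outcomes it states a method, and that method stops short of the objectives.

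Three things are at stake.

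1. With roughly 26 to 32 people per arm, the effect will be imprecise. If the interval is not reported, readers may take a point difference between two columns of means as a planning value.
2. If medians and IQRs are reported for an outcome, a mean difference with an interval does not follow directly from them, and neither does the SD needed to size the definitive trial.
3. The most economical way to gain precision, adjusting for a baseline value that is collected anyway, is not taken up.

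**Working it through.** **The plan's own figures.** The only precision figures are for feasibility rates (Sample size, n = 60). Using p ± 1.96 × √(p(1 − p)/60):

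- p = 0.50: 1.96 × 0.0645 = 0.1265, giving 37.35% to 62.65% (stated 37.3% to 62.7%).
- p = 0.80: 1.96 × 0.0516 = 0.1012, giving 69.88% to 90.12% (stated 69.8% to 90.2%).

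Both reproduce to within 0.1 point, so these figures contain no error. No precision is stated for any between-group effect.

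**Inputs for the between-group effect.** There are 32 per arm (Sample size: "sample size will be increased to 64 with 32 allocated to each arm"). The plan's 80% retention gives 0.80 × 32 = 25.6, about 26 per arm. The correlation r between baseline and follow-up is not in the document and is assumed at 0.3 to 0.7.

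**Formula.** The half-width of the 95% CI for a difference in means, in SD units, is t × √(2/n) without adjustment. It is t × √(2/n) × √(1 − r²) with the baseline as covariate. The degrees of freedom are 2n − 2 without adjustment. They are 2n − 5 with it, allowing one for baseline and two for the three strata.

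| n per arm | Unadjusted | r = 0.3 | r = 0.5 | r = 0.7 |
|---|---|---|---|---|
| 32 | 0.50 | 0.48 | 0.43 | 0.36 |
| 26 | 0.56 | 0.53 | 0.48 | 0.40 |

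Example, n = 26 and r = 0.5: unadjusted 2.009 × √(2/26) = 2.009 × 0.277 = 0.56; adjusted 2.012 × 0.277 × √0.75 = 0.48.

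**Gain.** The shortening is 1 − √(1 − r²), that is 4.6%, 13.4% and 28.6% for r = 0.3, 0.5 and 0.7. Equivalently, 32 per arm acts like 32/(1 − r²) = 35, 43 and 63 per arm.

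**On the pain scale.** With an assumed NPRS SD of 2.0 points (range 1.5 to 2.5) and 26 per arm, the half-width is ±1.11 points unadjusted (0.84 to 1.39). With r = 0.5 it is ±0.97 (0.72 to 1.21). The article's minimal important difference for NPRS is 1.5 points.

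**GROC.** GROC rates perceived change, so it has no baseline of its own and the gain above does not apply to it. To illustrate why an interval is needed, take the earlier trial's 8-week improvement proportions given in Background (77% EDX, 29% wait-and-see) with 26 per arm. The difference is 48 points and its SE is √((0.77 × 0.23 + 0.29 × 0.71)/26) = 0.121, so the 95% CI is about 24 to 72 points.

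**Strata.** The article gives no stratum effects, so the gain from adjusting for recruitment method cannot be computed.

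**The case against.** The strongest reply is that this is a feasibility trial whose primary outcomes are recruitment and retention, that descriptive reporting of secondary clinical outcomes is a defensible choice, and that a condensed article leaves the regression model and covariates to an analysis plan. Much of that stands. Silence about covariates alone would not be a finding. What it does not answer is that the article states a descriptive method beside objectives that ask for a comparison and an effect size.

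Several stronger readings are tempting, and the document does not support them.

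- *Objective 2 receives no between-group estimate at all.* The Sample size section commits to determining a between-group GROC effect, and Table 3 gives the time points. What is absent is the estimator and its interval.
- *A raw comparison would be invalid.* With 1:1 randomisation the unadjusted difference is unbiased, and its interval already allows for chance baseline imbalance. If means and SDs are given by arm, the difference, its CI and a planning SD all follow. Adjustment buys precision, not validity.
- *The strata are never used.* They are used for recruitment and retention rates. Only the clinical outcomes lack them.
- *The precision gain helps the outcome meant to power the definitive trial.* That outcome is GROC, and own-baseline adjustment is not available for it.

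**Conclusion.** The point holds in limited form. The article promises a comparison and a between-group effect, but its stated analysis of clinical outcomes is summaries by visit, with no difference, no interval and no use of baseline or strata. The planned imputation consequently has no named estimate to test. The objectives could still be met from by-arm means and SDs, so this is lost precision and an incomplete statement, not a fatal flaw.

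The size is a 95% CI shorter by about 5% to 29% for scales that have a baseline. This rests on an assumed correlation of 0.3 to 0.7 and on a linear relation with common slope and variance across arms. The NPRS figures rest further on an assumed SD of 1.5 to 2.5. No baseline gain can be claimed for GROC, and none can be quantified for the strata. The change is worth making because it costs almost nothing.

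**What to change.** In Statistical analysis, replace the sentence on clinical outcomes with a short paragraph stating that:

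1. each continuous outcome at 8 weeks and 3 months will be summarised by randomised group and reported with a between-group difference (EDX minus usual care) and 95% CI, without hypothesis tests;
2. the difference will be adjusted for recruitment stratum and, where one exists, the outcome's baseline value;
3. GROC will be reported as a between-group difference with 95% CI, adjusted for stratum;
4. the multiple imputation will be a sensitivity analysis of these estimates.

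The cost is one paragraph of wording. No new data, visits or participants are needed, and the feasibility outcomes are untouched.

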### Sample size

We will aim to recruit 64 participants. A sample of 60 participants (n=30 per arm of the trial) would provide an estimate of the recruitment rate of ≥50% (95% confidence interval (95% CI) 37.3% to 62.7%), and an estimated retention rate of ≥80% (95% CI of 69.8% to 90.2%). To ensure balance within each stratum, sample size will be increased to 64 with 32 allocated to each arm. This sample size will also allow for the potential effect of the primary outcome (GROC) between the two groups to be determined for powering a larger definitive trial.

Study status: is currently ongoing. The expected end date for the study is January 2025.

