Written consent will be obtained at the time of physical screening for pragmatic purposes, but full eligibility will be confirmed on the basis of the MRI results. Once participants complete the baseline assessment, they will be randomly allocated into one of two groups: (1) education and exercise programme (EDX-Ireland), or (2) usual care. Participants will complete the patient-reported outcomes (PROs) and abductor muscle strength assessment at baseline, 8 weeks, and 3 months.

Participants will be asked to refrain from other treatments during the trial period, but analgesia and anti-inflammatory drugs will be permitted. All medication use and co-interventions will be recorded
*via* the healthcare utilisation questionnaire.

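### The planned precision of the recruitment rate takes the 60 enrolled participants as its denominator, whereas the protocol defines the rate over eligible people approached; the stated interval is about 41% to 46% too wide, an error on the safe side

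*Protocol article*

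**What the plan says.** The Sample size section of the protocol article starts from "A sample of 60 participants (n=30 per arm of the trial") and says that this sample "would provide an estimate of the recruitment rate of ≥50% (95% confidence interval (95% CI) 37.3% to 62.7"%). It adds "an estimated retention rate of ≥80% (95% CI of 69.8% to 90.2"%). The total is then raised for balance within strata: "sample size will be increased to 64 with 32 allocated to each arm".

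The Statistical analysis section defines both rates:

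- Recruitment: "Recruitment rates will be calculated as the number of participants who consent to participate divided by the number of eligible participants approached".
- Retention: "Trial retention rates will be calculated from the number of participants who complete all outcome measures divided by the number who record baseline outcome measures".

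Both are to be reported as "percentages and 95% CIs". The section on outcome measures names recruitment and retention to 3 months as the focus of the primary outcomes. On timing, the Procedure section says: "Written consent will be obtained at the time of physical screening for pragmatic purposes"; full eligibility is settled later, by the MRI.

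**The concern.** The two rates have different denominators. Retention is a fraction of people who have entered the trial and given baseline data, so a sample of 60 is the right base for it. Recruitment is a fraction of eligible people approached, and those who join are its numerator. The Sample size section uses the same 60 for both. The recruitment interval therefore describes a proportion that the trial will not calculate.

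At stake is whether the written justification of the sample size is correct for one of the two primary feasibility outcomes. The rate is also meant to inform a definitive trial, so a planning calculation with the wrong base could be carried forward.

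**Working it through.** **Inputs.** From Sample size: 60 participants (30 per arm), final target 64, recruitment rate 50%, retention 80%, and the two stated intervals. From Statistical analysis: the two definitions and the 95% level. The documents do not give the expected number of eligible people approached, so it is derived below from the assumed rate.

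**Formula.** Wald 95% interval: p ± 1.96 × √(p(1 − p)/n).

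**Step 1. Reproduce the stated recruitment interval.** With p = 0.5 and n = 60: 1.96 × √(0.25/60) = 0.1265, giving 37.35% to 62.65%. This matches the stated 37.3% to 62.7%. Other candidates do not match: Wilson at n = 60 gives 37.7% to 62.3%, Clopper-Pearson at n = 60 gives 36.8% to 63.2%, Wald at n = 64 gives 37.7% to 62.3%, and Wald at n = 120 gives 41.1% to 58.9%. The denominator used was 60.

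**Step 2. Could 60 be the number approached?** At a 50% rate, 60 approached would yield 60 × 0.5 = 30 participants in total. The text says 30 per arm, so the 60 are enrolled people.

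**Step 3. Apply the protocol's own definition.** The denominator is the number recruited divided by the rate.

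| Recruited | Rate | Eligible people approached | Half-width (points) | 95% CI |
|---|---|---|---|---|
| 60 | 50% | 60/0.5 = 120 | 1.96 × √(0.25/120) = 8.9 | 41.1% to 58.9% |
| 64 | 50% | 64/0.5 = 128 | 1.96 × √(0.25/128) = 8.7 | 41.3% to 58.7% |

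The choice of method hardly matters here. At n = 120, Wilson gives 41.2% to 58.8% and Clopper-Pearson 40.7% to 59.3%.

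**Step 4. Size of the discrepancy.** Ratio of half-widths: √(120/60) = 1.41 and √(128/60) = 1.46. The stated interval is about 41% to 46% too wide.

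**Step 5. Dependence on the assumed rate.** The plan speaks of at least 50%. With 64 recruited:

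- 60% means about 107 approached, 50.7% to 69.3%
- 70% means about 91 approached, 60.6% to 79.4%
- 80% means 80 approached, 71.2% to 88.8%

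With the number recruited fixed at 60, the half-width is 1.96 × √(p²(1 − p)/60). This is largest at p = 2/3, where it is 1.96 × √(0.1481/60) = 9.7 points. Whatever the rate, it stays below the stated 12.7.

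**Step 6. Consent before MRI.** The numerator is people who consent, and some may be excluded after MRI. Consenters may then exceed those randomised, so 120 and 128 are lower bounds at a 50% rate. As an illustration (an assumption, not a figure from the documents), suppose one in five who consent is excluded. Then 64 randomised means 64/0.8 = 80 consenters and 80/0.5 = 160 approached. The half-width is 1.96 × √(0.25/160) = 7.7 points, or 42.3% to 57.7%.

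**The case against.** The best defence is that nothing depends on this figure. It is a planning interval; the observed rate and its confidence interval will be calculated under the definition in Statistical analysis, and the Sample size section ties no test or progression threshold to it. The error also understates the precision. All of that stands, and it limits the severity. It does not remove the contradiction, because the article itself states the sample, the interval and the definition, and they do not fit together. This is not detail left to another document.

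A reader might infer several further faults, which the documents do not support:

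- **Retention interval.** Wald at 80% and n = 60 gives 69.88% to 90.12%, against the stated 69.8% to 90.2%. Rounding outward to one decimal gives exactly the stated limits, and the same rule gives 37.3% to 62.7% from 37.35% to 62.65%. The base of 60 is of the right kind for retention.
- **Intervals at 60, not 64.** The text says openly that 64 was set afterwards for balance within strata.
- **The at-least signs.** They can be read as minimum anticipated rates with the interval evaluated at the minimum. No claim is made that a lower limit exceeds 50% or 80%.
- **No screening volume.** An article may leave this to the full protocol, and Table 3 records each stage from first contact to randomisation. Nor would 128 be a screening target: it counts eligible people approached, and three-phase screening would involve more people than that.

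**Conclusion.** The point holds in a limited form. The interval of 37.3% to 62.7% is correct arithmetic for 50% of 60, but 60 is not the denominator of the recruitment rate as the protocol defines it. At 50%, the interval consistent with the definition is about 41.1% to 58.9% for 60 recruited and about 41.3% to 58.7% for 64. The half-width falls from 12.7 points to 8.9 or 8.7.

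These figures assume a rate of exactly 50%, a Wald interval, and as many consenters as people recruited. If some who consent are excluded after MRI, the denominator at the same rate is larger and the interval narrower.

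A reader might conclude that the sample size is unjustified. It is not: the error is conservative, and 60 or 64 gives better precision for recruitment than claimed. This is a low to moderate correction to the text.

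**What to change.** In Sample size, separate the two rates. For recruitment, state the precision over the expected number of eligible people approached, for example: at an anticipated recruitment rate of 50%, recruiting 64 implies at least about 128 eligible people approached, with a 95% CI of about 41% to 59%. Add that this denominator depends on the assumed rate and is larger if some who consent are excluded after MRI. Present the figure as an expected denominator, not as a screening target. Use the enrolled sample as the denominator for retention only; that interval can stay as it is.

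The cost is a change of wording. Enrolment, design and the planned analysis are unaffected.
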